### Evaluation

An initial evaluation will include the collection of demographical and clinical variables will be performed at baseline. In addition, primary and secondary motor, cognitive and emotional well-being and quality of life outcomes will be evaluated before and after the intervention as well as at 3-month follow-up. Table 4 summarises the variables and outcomes of the study. Considering the current health crisis due to the COVID-19 pandemic, the evaluation will be carried out at the participant’s home in order to avoid unnecessary visits to the hospital.

**Table 4 Tab4:** Variables and outcomes of the study

Instrument	Reference	Baseline	Post-intervention	Follow-up

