**Demographic and clinical variables**				
Montreal Cognitive Assessment	[62]	•		
Digit span subtest	[97]	•		
Boston Naming Test, short form	[47]	•		
Vocabulary subtest	[97]	•		
Scale and rhythm subtests Montreal Battery of Evaluation of Amusia	[68]	•		
Barcelona Music Reward Questionnaire	[51]	•		
Grit scale	[23]	•		
Multidimensional Scale of Perceived Social Support	[95]	•		

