#### Baseline demographic and clinical variables

Demographic and clinical variables such as age, gender, level of education, living situation, previous musical training, stroke aetiology and location, and lesion laterality will be collected from medical records as well as during a first interview with the participant.

In order to characterise individual differences that can have a mediating effect on treatment success, we will evaluate cognitive functions, differences in the processing and integration of music, music reward, perseverance and social support at the beginning of the intervention. Therefore, the baseline evaluation will include the Spanish version of the *Montreal Cognitive Assessment* [45, 62] to assess global cognitive function, the *digit span* (included in the *Wechsler Adult Intelligence Scale,* WAIS-IV, [97]; adapted to Spanish by Pearson Clinical & Talent Assessment) to assess working memory, a short version of the *Boston Naming Test* validated in Spanish [14, 47] to assess language production, and the *vocabulary subtest* of the WAIS-IV. In addition, the *scale* and *rhythm subtests* from the shortened version of the *Montreal Battery of Evaluation of Amusia* [68] will be used to screen for amusia at baseline. Participants will complete the *Barcelona Music Reward Questionnaire* ([51], validated in Spanish) on the first evaluation to assess individual differences in pleasure derived from musical experiences. Finally, individual differences in perseverance and passion for long-term goals will be assessed with the *Grit Scale* ([23]; validated in Spanish in [9]), and social support will be assessed using the Spanish version of the *Multidimensional Scale of Perceived Social Support* ([43, 95]).

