### Sample size

The sample size calculation is based on a clinically relevant difference between treatment groups with 80% power and a 5% significance level. Considering that the minimal detectable change of the ARAT (primary outcome) is 5.7 points and that an acceptable difference between groups of 15% is defined to be clinically meaningful [84, 85], a sample size of 26 participants will be required in each group. From experience gathered in previous studies [32, 77], the dropout rate in this type of interventions is relatively low (15%). Taking this rate into consideration, a final estimation of 60 participants is needed in the study, 30 per group.

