### Data analysis

Statistical analysis will be performed using *R* (R Core Team, 2019) and the *Statistical Package for the Social Sciences* (SPSS version 21, SPSS inc., Chicago, Illinois, USA). For descriptive analyses, quantitative data will be analysed using mean and standard deviation if the data is normally distributed and median and interquartile range will be used for variables that are not normally distributed. Qualitative variables will be presented using frequency distributions and percentages.

An intention-to-treat analysis will be performed for all outcome variables including all patients that were assigned to a group and for whom the primary outcome was collected at baseline. In the case of participants that withdraw form the study, the score at baseline will be assigned for all the evaluation points and reasons for withdrawal will be reported.

The effect of the intervention on the primary outcome, the ARAT, will be assessed using the chi-square test. Taking into account the minimal clinically important difference of this test (5.7 points) data will be dichotomized into two categories: *clinically improved* or *unchanged/deteriorated.* An analysis of covariance (ANCOVA) will be carried out for all secondary outcomes to determine differences between groups across time using demographical and clinical baseline variables as covariates. The level of significance will be set at *p* < 0.05 for all statistical tests and corrected for multiple comparisons when necessary.

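### The ANCOVA for the secondary outcomes names demographic and clinical covariates but not the baseline value of the outcome being analysed

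*Protocol article*

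**What the plan says.** The Data analysis section of the protocol article plans an ANCOVA for all secondary outcomes "to determine differences between groups across time using demographical and clinical baseline variables as covariates". It gives no list or number of covariates and does not mention the baseline value of the outcome.

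The article uses the covariate label elsewhere:

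- The section on baseline demographic and clinical variables names eight items from records and interview: "Demographic and clinical variables such as age, gender, level of education, living situation, previous musical training, stroke aetiology and location, and lesion laterality". The list is open-ended.
- Table 4 has a block headed "Demographic and clinical variables" with eight instrument rows: Montreal Cognitive Assessment, digit span, Boston Naming Test, vocabulary, two amusia subtests in one row, music reward, grit and social support.
- The purpose given for these instruments is not precision: "In order to characterise individual differences that can have a mediating effect on treatment success".
- The Evaluation section introduces the outcomes as a further set. These "outcomes will be evaluated before and after the intervention as well as at 3-month follow-up", and Table 4 places them under separate outcome headings.

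**The concern.** In a randomised trial with a baseline and a later measurement of the same scale, the baseline score is normally the covariate that removes most outcome variance and corrects chance imbalance on that scale. Here the article names a covariate class whose members, by its own headings, do not include that score. It does include many variables with no obvious link to, say, grip strength or pegboard time.

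With about 60 patients both features matter. Precision available from a score that is already scheduled may go unused, and degrees of freedom may be spent on weak predictors. If only some of the listed variables are to enter, the text does not say which, and they could be chosen after results are seen. The effect is confined to the secondary outcomes.

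**Working it through.** There is no figure in the article to reproduce here: it gives no correlation, SD or R² for any secondary outcome. The correlations r below are assumptions.

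**1. Is the outcome's baseline value in the named class?** The Evaluation section mentions demographic and clinical variables first and then adds the outcomes. Table 4 keeps the two under different headings. The section on ethics and data management also lists them as two things. On the natural reading the answer is no.

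**2. Cost of not conditioning on baseline.** Assume equal variance at baseline and post, 1:1 allocation, and no effect of randomising in clusters of three. Relative to unadjusted post values (variance 1):

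- baseline-adjusted: 1 − r²
- change from baseline: 2(1 − r)
- change over adjusted: 2(1 − r)/(1 − r²) = 2/(1 + r)
- post only over adjusted: 1/(1 − r²)

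| r | adjusted | change | change ÷ adjusted | post only ÷ adjusted |
|---|---|---|---|---|
| 0.5 | 0.75 | 1.00 | 1.33 | 1.33 |
| 0.7 | 0.51 | 0.60 | 1.18 | 1.96 |
| 0.8 | 0.36 | 0.40 | 1.11 | 2.78 |

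Estimating the one baseline slope at n = 60 multiplies the adjusted variance by 57/56 = 1.018, giving 0.76, 0.52 and 0.37, so the picture does not change. In sample-size terms, 60 patients analysed as change scores have the precision of about 60/1.33 = 45, 60/1.18 = 51 or 60/1.11 = 54 patients analysed with baseline adjustment.

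**3. Number of candidate covariates.** Eight record and interview items plus eight Table 4 rows make 16, or 17 if the two amusia subtests count separately.

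**4. Cost of entering them.** With k single-degree-of-freedom covariates that jointly explain R² of the outcome variance, the variance of the group difference, relative to leaving them out, is (1 − R²)(N − 3)/(N − 3 − k). The Data analysis section includes everyone with a baseline primary outcome and assigns the baseline score to withdrawals, so N stays near 60.

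- k = 17, R² = 0: 57/40 = 1.425. Simulation of 6,000 trials gave 1.40. The standard error rises by about 19%.
- k = 16, R² = 0: 57/41 = 1.39.
- k = 8, R² = 0: 57/49 = 1.16.
- Break-even for k = 17: R² = 1 − 40/57 = 0.30. Above this the covariates help.
- k = 17 at R² = 0.1, 0.2, 0.4, 0.5: 1.28, 1.14, 0.86, 0.71.

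**The case against.** - **Baseline may be used after all.** The phrase about differences across time fits a repeated-measures model with baseline as one time level, so that the group-by-time contrast works on change. Many statisticians would also take ANCOVA in a trial to imply baseline adjustment. This stands in part: the omission is an inference from the headings, not an explicit exclusion. Under the change-score reading the loss is the smaller set, 1.33, 1.18 and 1.11, but it is not nil.

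- **Covariate detail belongs in an analysis plan.** An exact list and coding could properly be left there. But the article is not silent: it names the class, and the class leaves out the most useful member.

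- **The count is not the plan's.** The article does not say that all listed variables enter, and nine of the 17 scores are there for another stated purpose. With the eight record and interview items alone, the maximum cost is 16%. Nor are the variables pure noise: age, education, digit span and vocabulary plausibly predict verbal learning, fluency and executive function. This objection stands, so the 43% is a ceiling. The 30% break-even, however, compares with no adjustment. To match the baseline score alone, 17 covariates would need a joint R² of 1 − 0.763/1.425 = 0.46, 1 − 0.519/1.425 = 0.64 or 1 − 0.366/1.425 = 0.74 at r = 0.5, 0.7 or 0.8.

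- **A stronger reading is tempting.** A reader might infer that the plan adjusts for 17 variables and ignores baseline, and multiply the two losses: 1.33 × 1.425 = 1.9, 1.96 × 1.425 = 2.8, 2.78 × 1.425 = 4.0. That needs all 17 to enter, none to explain anything, and post values alone to be analysed. The article states none of these, and its wording about time speaks against the last.

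**Conclusion.** The point holds for the secondary outcomes. The stated covariate class does not, on the article's own headings, contain the baseline value of the outcome, and using that value would improve the stated analysis at no cost in data. The variance penalty for not conditioning on it is 1.33, 1.18 or 1.11 times under a change-score analysis and about 1.3, 2.0 or 2.8 times under a post-only analysis, at assumed correlations of 0.5, 0.7 and 0.8. The wide covariate class could add up to 43% (all 17) or 16% (eight items), falling to nothing or becoming a gain as joint R² rises past about 0.30 for the 17, or 1 − 49/57 = 0.14 for the eight.

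The documents do not show that the covariates lose more precision than they gain, because no R² is given. Nor do they show that 17 will be entered. The primary outcome, a chi-square test on dichotomised ARAT change, has no covariates and is not touched. This is a change worth making, not a flaw that undermines the trial's main comparison.

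**What to change.** In the Data analysis section, state for every secondary outcome measured at baseline and at follow-up that the model adjusts for the baseline value of that same outcome. Add at most a short list of further covariates, named with their coding before any outcome data are seen by arm. One ANCOVA per follow-up visit or a single repeated-measures model would both serve, provided the choice is stated.

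Keep music reward, grit and social support for analyses labelled exploratory, as covariate-by-arm interactions. This fits the article's stated interest in individual differences that may modify the effect.

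Three questionnaires fall outside this change because each is given only once: treatment self-regulation at the start, continued participation at week 5 and intrinsic motivation at the end. The self-efficacy questionnaire, which its section says is given before and after the intervention, falls inside it for the post-intervention value.

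The cost is an edit to the analysis text. The baseline scores are already scheduled in Table 4, so no visit, instrument or patient is added.

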### Trial registration

The trial has been registered at ClinicalTrials.gov and identified as NCT04507542.

## Discussion

Chronic stroke patients with residual motor deficits experience limitations in activities of daily living and restrictions in participation in community life [35]. The impact of these residual motor deficits on function coupled with low levels of physical activity can lead to poor emotional well-being, life satisfaction and quality of life [12, 38]. There is increasing interest in developing home and community-based interventions for chronic stroke patients to address their needs and improve their autonomy, participation and overall well-being [13, 34].

MST aims at improving motor and cognitive functions, emotional well-being and quality of life in stroke patients and could be a feasible intervention to apply in the chronic phase [32, 71, 79]. We have adapted the original MST program for home use and we have increased training intensity and variability, incorporated group sessions, and modified the protocol to boost learning by enhancing motivation and promoting more autonomy. The incorporation of these changes and the adaptation of the program take into account the Medical Research Council Framework for Developing and Evaluating Complex Interventions. In order to further develop MST we identified relevant evidence in the literature and developed a theoretical understanding of the processes of change [33]. Moreover, we have modelled the intervention process and outcomes, and assessed feasibility with a pilot study.

The study has been designed following the CONSORT guidelines for conducting clinical trials. The evaluation protocol includes baseline variables such as social support, perseverance or musical reward to take into account individual differences that may modulate the treatment effect. The outcomes of the study address various dimensions of functioning, with instruments that evaluate body functions, activity and participation. In addition, we have included measures of self-regulation and self-efficacy. Considering that the intervention is home and community-based, these factors may have a crucial role in treatment adherence and success.

We expect that patients treated with eMST will show larger functional improvements than patients treated with the control therapy regimen. On the basis that MST improves several dimensions of functionality beyond the motor function, we expect that patients will improve their mood and emotional well-being after MST.

## Data Availability

Data and materials can be accessed by contacting the corresponding author and in the research group webpage: https://www.brainvitge.org

## Abbreviations

AI: Artificial intelligence
ARAT: Action Research Arm Test
BRIEF: Behaviour Rating Inventory of Executive Function
eMST: Enriched Music-Supported Therapy
FMA: Fugl-Meyer Assessment of Motor Recovery after Stroke
GRASP: Graded Repetitive Arm Supplementary Program
MST: Music-Supported Therapy
MTCSI: Music Therapy Communication and Social Interaction scale
